### Secondary endpoints

The secondary endpoints were selected to provide supportive information on safety and efficacy. These secondary endpoints include:

Postoperative rebleeding associated with deterioration following MIPS (no hypothesis test).ICU and in-hospital length of stay (two-sided *t*-test).mRS at discharge, 30 and 90 days (ordinal logistic regression; treatment as explanatory variable).Impact of percent ICH reduction with MIPS on mRS at 180 days (ordinal logistic regression; %ICH reduction as explanatory variable).Impact of end-of-treatment (EOT) volume with MIPS on mRS at 180 days (ordinal logistic regression; EOT volume as explanatory variable).Proportion of patients with mRS at 180 days equal to 0, 1, 2, or 3 (chi-square test).Ordinal mRS at 180 days (Wilcoxon rank sum test).Overall survival through 180 days (log-rank test and Cox proportional hazards model).

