## Methods and analysis

### Study objective

The primary objective of the ENRICH trial is to determine if early ICH evacuation using MIPS results in improved outcomes for patients with an ICH. The primary hypothesis is that MIPS will result in an improvement in the 180-day utility-weighted modified Rankin Scale (UWmRS) when compared to patients treated with standard guideline-based management. To address the primary objective, we have designed an adaptive clinical trial with a sample size between 150 and 300 subjects, with frequent interim analyses to determine if early stopping rules are met and if patient population enrichment per hemorrhage location should occur. Randomization between MIPS and standard management groups will be equal and patients will be block randomized by ICH location, anterior basal ganglia (ABG) vs. lobar location as well as Glasgow Coma Score (GCS) with a threshold for stratification <9 vs. ≥9. At each interim analysis, the enrollment scheme defined by hemorrhage location can be adapted based on the *a priori* enrichment plan.

Secondary aims of the study will evaluate the economic and clinical benefits, and the safety of MIPS compared to standard management. The clinical benefit of MIPS is thought to be a function of clot removal while minimizing white matter injury. Therefore, we will determine if the percent volume of ICH reduction is associated with improved UWmRS at discharge, 30, and 90 days between the treatment groups. The economic effect of MIPS for ICH will be evaluated by quantifying the cost per quality-adjusted life-year (QALY) gained through MIPS at 30, 90, 120, and 180 days. Safety of MIPS will be assessed: (1) by determining the effect of MIPS on mortality when compared to standard management at 30 days; (2) by assessing post-operative rebleeding associated with clinical deterioration following MIPS. Rebleeding will be defined by a growth in hemorrhage volume between an initial non-contrast head computed tomography scan (NCCT) and a follow-up NCCT obtained within 24 h of the index NCCT. Lastly, we will evaluate the impact of time from onset of symptoms to MIPS on the UWmRS.

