**ASSESSMENTS**									
Neurologic evaluation, lab, neuroimaging, CSG checklist									
ICH reduction in association with improved UWmRS					x	x	x		x
Economic effect: QALY						x	x.	x	x
Adverse event monitoring	x				x	x	x	x	x
Safety: mortality									
Safety: rebleeding			x						
mRS	x					x	x		x
HUI						x	x	x	x
NIHSS and GCS	x			x	x				x

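### The percent-reduction and end-of-treatment-volume models name one post-surgical predictor and no baseline severity; separately, the clot-reduction analysis is specified three different ways

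*Protocol article*

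**What the plan says.** Under Secondary endpoints, the protocol article names the model for each of two analyses: "Impact of percent ICH reduction with MIPS on mRS at 180 days (ordinal logistic regression; %ICH reduction as explanatory variable") and "Impact of end-of-treatment (EOT) volume with MIPS on mRS at 180 days (ordinal logistic regression; EOT volume as explanatory variable"). Neither entry names a baseline term. The same section describes the role of the list: "The secondary endpoints were selected to provide supportive information on safety and efficacy".

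The clot-reduction question also appears in two other places. Under Study objective: "we will determine if the percent volume of ICH reduction is associated with improved UWmRS at discharge, 30, and 90 days between the treatment groups". In the assessments block of Table 1, the row "ICH reduction in association with improved UWmRS" is marked, as extracted, at discharge, 30, 90 and 180 days.

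Two further statements matter here. Eligibility (Table 2) admits baseline volumes of 30 to 80 ml and GCS 5 to 14. The rationale for the eligibility criteria treats volume as prognostic: reasonable outcomes are expected in many patients below 30 ml, and dismal ones often above 80 ml.

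**The concern.** Both predictors are observed after surgery, and nobody is randomised to a level of either. A patient who starts with 80 ml and has 80% removed is left with 16 ml (80 × 0.20); one who starts with 30 ml and has the same 80% removed is left with 6 ml (30 × 0.20). If larger haemorrhages do worse whatever is done, less residual clot will go with better outcome even when removal has no effect.

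The Study objective section presents clot removal as the presumed source of the MIPS benefit and derives this analysis from that idea, and the endpoint list words both analyses as an impact. A significant coefficient is therefore likely to be read as evidence of mechanism, which an unadjusted model cannot carry.

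The second issue is independent of the first. If the scale, time points and population of one analysis differ by section, the version to report can be chosen after the data are seen.

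**Working it through.** **No stated figure to reproduce.** The article gives no power, alpha or sample size for these analyses. Total enrolment of 150 to 300 with equal allocation gives 75 to 150 MIPS patients.

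**EOT volume, closed form.** From the document: baseline volume V between 30 and 80 ml. Assumed: V uniform; residual fraction R with mean 0.20 and SD s = 0.10 to 0.15, independent of V; outcome driven only by V, with an odds ratio of 1.15 to 1.4 per 10 ml for worse mRS; no effect of evacuation.

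- V has mean 55, variance 50²/12 = 208.3 and SD 14.43.
- With E = V × R, Cov(V, E) = 0.20 × 208.3 = 41.7.
- Var(E) = (55² + 208.3)(0.20² + s²) − (55 × 0.20)².
  - s = 0.10: 3233.3 × 0.05 − 121 = 40.7, SD 6.38, correlation 41.7/(14.43 × 6.38) = 0.45.
  - s = 0.15: 3233.3 × 0.0625 − 121 = 81.1, SD 9.00, correlation 41.7/(14.43 × 9.00) = 0.32.
  - In simulation the correlation is 0.35 to 0.46.
- Log odds ratio per SD of V: 1.443 × ln 1.4 = 0.486, or 1.443 × ln 1.15 = 0.202.
- Spurious log odds ratio per SD of E, approximately correlation × that value: strongest 0.45 × 0.486 = 0.22 (OR 1.25); weakest 0.32 × 0.202 = 0.065 (OR 1.07).
- z = slope × √[n(1 − Σp³)/3]. With seven equally likely categories, Σp³ = 7 × (1/7)³ = 0.020, so the root is 7.00 at n = 150 and 4.95 at n = 75.
- Strongest: z = 1.54 and 1.09, rejecting in about 34% and 19%. Weakest: z = 0.45 and 0.32, rejecting in about 7% and 6%.

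Simulation under these inputs gives 8-31% at n = 150 and 5-20% at n = 75, which agrees with the approximation. With baseline volume in the model the rate is 4-6%.

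**Both predictors, with GCS also prognostic.** A second simulation fitted proportional-odds models with likelihood-ratio tests, 400 runs per cell and again no evacuation effect. Assumed: volume uniform 30-80 ml and GCS uniform 5-14, each shifting the mRS log-odds by 0.5 per SD; mean residual 20%, SD 12 points; correlation of severity with residual fraction −0.3, 0 or +0.3.

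| Predictor alone | Sicker patients keep | Rejects, n = 75 | Rejects, n = 150 | OR of worse mRS per SD |
|---|---|---|---|---|
| % reduction | same fraction | 6% | 6% | about 1.0 |
| % reduction | larger fraction | 17% | 34% | about 0.8 |
| % reduction | smaller fraction | 16% | 32% | about 1.2 |
| EOT volume | same fraction | 15% | 29% | about 1.21 |
| EOT volume | larger fraction | 40% | 64% | 1.44, 1.41 |
| EOT volume | smaller fraction | 7% | 7% | 1.03, 1.02 |

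With baseline volume and GCS added, every cell falls to 4-9%, with odds ratios of 0.98 to 1.03.

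**The three specifications of the clot-reduction analysis.**

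| Place | Scale | Time points | Population |
|---|---|---|---|
| Study objective | UWmRS | discharge, 30, 90 days | between treatment groups |
| Table 1 | UWmRS | discharge, 30, 90, 180 days | not stated |
| Secondary endpoints | ordinal mRS | 180 days | with MIPS |

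Table 1 covers all the time points but does not settle the scale or the population.

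**The case against.** The best defence is that these are supportive analyses, that an analysis plan not shown here may add covariates, and that the Study objective already speaks of association. The first part stands and limits the weight of the point. The second is possible, but the article does more than stay silent: it states the model and names one explanatory variable for each. The third is only partly met, because the endpoint list speaks of impact.

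It is also fair that the size rests on assumed prognostic strength and assumed spread of evacuation, and that at 75 patients, or if sicker patients keep a smaller fraction, the inflation is small or absent.

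Three stronger readings are tempting and are not supported:

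- That the models would credit evacuation with the effect of severity. For percent reduction the bias is nil if reduction is unrelated to severity and can run for or against evacuation if it is related. The article does not say which applies.
- That the timing analysis has the same defect. It appears as one sentence, "Lastly, we will evaluate the impact of time from onset of symptoms to MIPS on the UWmRS", with no model, covariates or time point. It cannot be shown to be unadjusted or contradictory, and missing detail in a condensed article is not an error. A treatment-by-time interaction would answer a different question.
- That the inconsistent specification causes the confounding. It does not; it leaves open which result will be reported.

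**Conclusion.** The point holds in limited form. As written, both models rest on a single non-randomised, post-surgical predictor. For EOT volume the link to baseline volume is arithmetical, and the false-positive rate is about 8-31% with 150 MIPS patients and 5-20% with 75, against 4-6% after adjustment for baseline volume. That is conditional on an odds ratio of 1.15 to 1.4 per 10 ml, 80% mean evacuation with an SD of 10 to 15 points, and a residual fraction independent of baseline volume. For percent reduction the risk is conditional on a relation to severity that the article does not state, and its direction is unknown.

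The conflict between Study objective, Table 1 and Secondary endpoints on scale, time points and population is a separate defect and needs no assumption. The primary intention-to-treat comparison and its success rule are unaffected. The change is worth making because it costs almost nothing.

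**What to change.** 1. Add baseline ICH volume, GCS, location and age to both ordinal logistic models.
2. Report the coefficients as associations, and replace the wording that calls them an impact of reduction or of EOT volume.
3. State one scale, time point and population for the clot-reduction analysis and use it in Study objective, Table 1 and Secondary endpoints. One option is ordinal mRS at 180 days within the MIPS arm, which follows the Secondary endpoints entry.

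The cost is a few model terms and consistent wording. Volume, GCS, location and age are already needed for eligibility or stratification, so no new data are required. Adjustment removes confounding only by the covariates included, so the association label stays necessary afterwards.

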### Economic outcome analysis

The ENRICH economic evaluation will assess the primary endpoint: the relative cost-effectiveness of MIPS vs. standard management at 180 days with the effect measured in terms of quality-adjusted life-years (QALYs). QALYs will be calculated from the results of the HUI. Secondary analysis will also: (1) inform how adoption of MIPS will intersect with new and forthcoming Medicare reimbursement policies; and (2) provide evidence on clinical cost-effectiveness.

For the primary endpoint, an incremental analysis will be undertaken to determine the cost per QALY gained through MIPS calculated as: (C_MIP_ – C_std_)/(QALY_MIP_ – QALY_std_) where C_I_ = cost per treatment arm and QALYI = QALYs per treatment arm.

### Safety monitoring

At each Data and Safety Monitoring Board (DSMB) meeting, members will be presented with group comparisons with respect to mortality, occurrence of rebleed and hemorrhage expansion, unexplained and unexpected surgical complications, and other SAEs. The DSMB will also be presented group A–B comparative rates of adverse events to identify any unexpected trends.

An independent medical monitor (MM) will review every SAE for causality and expectedness. For events that are deemed potentially high-risk for future subjects, the DSMB will be provided a report and any necessary additional A–B analysis to make recommendations about study continuation.

The DSMB is a fully independent group of experts selected to advise the ENRICH leadership team, site investigators, and study sponsor and to periodically review and evaluate study data for participant safety, study conduct and progress, and efficacy.

### Rationale for early treatment window

The pathophysiology of ICH is time-dependent; therefore, subjects enrolled in ENRICH and randomized to MIPS will have surgery within 24 h of LKN, with a goal of 8 h. Following the initial ICH, a secondary cascade of inflammation-mediated and pro-apoptotic signaling pathways is initiated, contributing to the poor outcomes (13–15). Previous attempts at ultra-early intervention showed discouraging results using conventional craniotomy (19, 20). Collateral damage of eloquent tissue during surgery remained an important challenge in these studies in addition to poor visualization, and suboptimal hemostasis, all of which we hypothesize have been improved upon with MIPS. Considering the preclinical biological evidence available, a time window of 24 h will allow for early intervention and facilitate institutional and logistic support.

### Rationale for specified eligibility criteria

Eligibility criteria were formulated to investigate a population of ICH patients with high risk for poor outcomes that may also benefit from intervention experiencing a significant event unrelated to a vascular anomaly (21, 22). Patients with a hemorrhage volume <30 ml may benefit from MIPS but any observed relative benefit is likely to be small in magnitude as many of these patients may have reasonable outcomes with supportive medical care. Patients with hematoma volume exceeding 80 ml often have dismal outcomes and poor presenting exams limiting the expected benefit of this intervention. Additionally, clot evacuation for hemorrhages exceeding 80 ml is generally believed to be life-saving and functional improvement is rarely observed (12).

Primary thalamic hemorrhages have been excluded, despite the potential benefit from MIPS, for two principal reasons: (1) thalamic hemorrhages frequently lead to significant midbrain injury, and (2) hemorrhages in this location often have delayed recovery extending beyond 180-days (23).

Direct oral anticoagulants (DOAC) that cannot be reversed are necessarily excluded from the ENRICH trial due to potential untoward risk of hemorrhage expansion and rebleeding. FDA has recently approved agents for reversal of anticoagulation effects of some DOACs (24, 25), as a result, ENRICH excludes patients based on the ability to reverse the effect of the direct inhibitors.

### Rationale for randomization

Randomization minimizes the influence of bias often seen in observational studies of existing therapies. The MIPS technique uses the FDA-cleared BrainPath^®^ and Myriad^®^ (NICO Corporation Indianapolis, IN) devices. Both tools are widely available and have been used in over 40,000 cases of different neurosurgical pathologies including primary and metastatic brain tumors among several others (internal communication, NICO Corporation). Despite this reality, superiority to well-instituted standard management has not yet been established. Therefore, randomization is an ethical and rigorous tool in understanding the potential benefit that MIPS may offer.

### Rationale for the enrichment strategy

Lobar and deep ABG hemorrhages behave differently in prior surgical studies. The STICH trial suggested that more superficial hemorrhages might respond favorably to clot removal in the absence of intraventricular hemorrhage (19). While this hypothesis was not supported in the subsequent STICH II trial, it remains biologically plausible that access to superficial clots may result in less iatrogenic injury (7). As such, we decided to handle these two distinct hemorrhage groups separately so that if we established futility in one group, the investigation into the relative benefits of the other may proceed.

### Rationale for preventing cross over to MIPS

Intentional cross-over from standard management to MIPS is not permitted in this trial. Deteriorating subjects, regardless of randomization assignment may be provided the most aggressive life-saving care available. The most recent national guidelines in the care of the ICH patient detail Class IIb evidence for surgical clot evacuation, decompressive craniectomy, or the combination in the life-saving care of the ICH patient. These procedures, done under traditional techniques may be performed at the discretion of the clinical team, regardless of randomization assignment.

### Rationale for blinded adjudication of outcome

Because this study includes surgical intervention, outcomes cannot be reasonably performed in a blinded manner due to evidence of surgery. Therefore, a unique blinded adjudication process for the mRS was designed to minimize the effect of bias on the primary outcome. The ENRICH team enlisted an experienced Neuropsychologist, who is blinded to treatment allocation, to review audio recordings of subject mRS interviews. Following review of the audio recording the Neuropsychologist enters their assessment into the EDC. Discordance in the mRS value between the site and the Neuropsychologist are adjudicated by case discussion between the blinded and unblinded assessors. The final determination is made by the blinded Neuropsychologist.

### Rationale for cost per quality-adjusted life year gained assessment

ICH is a condition with high morbidity, and often early fatality rate. Should the MIPS approach be superior to standard management it is likely that cost of care of ICH patients may increase in the acute setting, even though the procedure may impact ICU length of stay, ICU-related complications, in-hospital length of stay, or length and complexity of post-acute rehabilitation, all of which may result in overall decreased cost in the long term. By utilizing the QALY metric, the cost can be analyzed in the context of patient outcomes. By convention, an intervention is deemed cost-effective if the treatment is in the range of $100,000–200,000 per QALY gained.

### Rationale for the primary outcome and follow up period

Patient-centered outcomes in stroke research are increasingly desirable. The utility is a measure that expresses the desirability of a specific outcome to a patient. The UWmRS converts the arbitrarily distinguished mRS to a patient-centered scale with distances between the items that better reflect societal and patient beliefs of the desirability of a particular outcome (26). The use of UWmRS also improves statistical efficiency when compared to the ordinal mRS. Statistical analysis of the ordinal mRS often leads to dichotomizing the outcome, reducing the power to detect treatment effects through collapsing important categories of health outcomes, or ordinal analysis, which does not account for the varied importance represented in the distance between each of the categories. The UWmRS may be analyzed as a continuous measure allowing the full use of the obtained data.

A 6-month follow-up term for the primary outcome was selected with the understanding that ICH survivors may continue to improve up to a year or more after the event. ICH trials have moved to a 6-month outcome and we have selected a similar outcome to permit comparison between trials.

### Rationale for site selection

Participating sites have been carefully selected based on prior experience with the MIPS approach, annual ICH volume, partnership between neurocritical care and neurosurgery, and experience of the research team. Selected sites are visited in person by a member of the Scientific Leadership Team (SLT) as well as for Site Initiation Visits prior to full engagement. A minimum of 10 sites will be involved in this study.

### Study organization and funding

Trial design, leadership, and conduct are overseen by the SLT at Emory University and representatives of the sponsor. Berry Consultants supports the SLT with the study's adaptive clinical trial design and one unblinded statistician (BS) performed the interim analyses. The trial sponsor and funder is the NICO Corporation. The sponsor will perform monitoring at all sites to ensure data quality and integrity, and the protection of the rights and safety of subjects through a contract research organization (IQVIA).

## Discussion

### Generalizability

The ENRICH clinical trial has been designed to enhance the care of ICH patients. The overall stroke community is desperately seeking an effective treatment for ICH that directly results in improved functionality. The broad inclusion criteria were designed to focus on those ICH patients with high risk of significant morbidity and mortality. This selection represents a large number of ICH patients and a cohort in whom scientific progress is imperative. Exclusion criteria were also selected with three guiding principles: (1) In whom might early clot evacuation prove beneficial? (2) In whom might the MIPS approach prove harmful? and (3) The ethical imperative to complete the trial with a fullness of scientific understanding that permits the improvement of care of these patients.

The ENRICH trial and the MIPS approach being studied is not being tested for every patient with an ICH, but rather a cohort of patients in whom the risk-benefit profile might lead to overall improvement.

### Expected impact of the proposed trial

There are no Level I evidence-based surgical options in the acute management of ICH. This trial is designed to determine if MIPS for ICH evacuation, performed within 24 h from LKW, results in improved functional outcome and economic benefit. Surgical evacuation following spontaneous ICH is an appealing treatment option; nonetheless, when studied, surgery has not been observed to be efficacious. It is believed that previous negative studies were due in part to trauma that occurs with accessing the ICH, heterogeneity in surgical and medical care, and patient selection. The ENRICH clinical trial improves upon these limitations with technology that permits access to deep structures with minimal trauma. This trial will significantly contribute to scientific literature guiding the optimal management of these medically complex patients.

## Dissemination

The trial results will be disseminated through publications in peer-reviewed journals, presentations at scientific conferences, and media channels.

The datasets generated during the study will be available upon reasonable request.

## Ethics statement

The studies involving human participants were reviewed and approved by Emory University Institutional Ethical Review Boards. The patients/participants provided their written informed consent to participate in this study.
